**Methods/Design:**

A prospective, randomized, single-blinded trial will be conducted. We will include 120 patients, 80 years of age and over with an acute (<36 h) displaced femoral neck fracture. The patients will be randomized in a 1:1 ratio to either total hip arthroplasty or hemiarthroplasty. The primary endpoints are Harris hip Score and EQ-5D. Secondary endpoints include pain measured with visual analogue scale, surgical time, reoperations, complications and radiological measurement of erosion in patients operated with hemiarthroplasty. Follow-up will be performed postoperatively after three months, 1, 2, 4 and 10 years.

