**Fig. 1 Fig1:**
[figure not shown]
Flow diagram

We hypothesized that a total hip arthroplasty results in superior hip function and health-related quality of life compared to to hemiarthroplasty in healthy and cognitively intact patients aged above 80 years treated for a displaced femoral neck fracture. The secondary outcome measurement includes mortality, complications and reoperations.

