### Endpoints and follow-up

The primary endpoint variable will be patient-reported functional hip status assessed with Harris hip score [23–25] and health related health-related quality of life assessed by the EQ-5D (EuroQoL) at 2 years. EQ-5D uses five dimensions: mobility, self-care, usual activity, pain/discomfort and anxiety/depression [26].

Secondary endpoints include functional scores at the other follow-up times and pain in the operated hip evaluated with VAS (Visual Analogue Scale [27], surgical time and blood loss, erosion of the acetabular cartilage in patients treated with hemiarthroplasty (evaluated according to Baker et al. [11]).

The study period is 10 years. Follow-up will be performed at 3 months, 1, 2, 4, 6 and 10 years. First study results will be reported after the last patient enrolled in the study has been followed for 2 years.

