### Sample size

Prior to the commencement of the study, a two-sided power analysis has been performed. We will test the null hypothesis that the mean Harris hip scores for the two groups will be equal. We assume that a mean difference of 10 points (standard deviation, 15 points) [4] in the Harris hip score is the smallest effect that will be clinically relevant. We calculate that a total of 80 patients (40 in each group) will have a power of 80 % to yield a significant result.

This calculation also allows a 80 % power to prove non-inferiority (non- difference) of the secondary endpoint EQ-5D with a sample of 40 patients in each group with the assumption of an EQ-5D value of 0.73 with standard deviation 0:18. The significance level was set at a conservative 2.5 % (p <0.025) because we have two sample size calculations. We will include 60 patients in each group (120 total) to allow for loss to follow-up.

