### Patient reported outcome measurements

The trial’s main outcome measurements are Harris hip score and EQ-5D. Both of these are valid measurements and has been used in an number of hip fracture trials.

Although Harris hip score has been questioned due to ceiling effect and may be inferior to WOMAC and HOOS as a disease specific questinnaire, this has not been confirmed in the hip fracture population [28–30]. The use of HHS also makes comparisons to other trials easier and it has been validated for the use in patients with a femoral neck fracture [30].

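### EQ-5D is a primary endpoint in three places and secondary where alpha and sample size are set, so the success rule is not fixed and 40 per group misses 80 % power at the printed 2.5 % level

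*Protocol article*

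**What the plan says.** Three places treat EQ-5D as primary or main. The Abstract (Methods/Design) says "The primary endpoints are Harris hip Score and EQ-5D". Endpoints and follow-up includes, within the primary endpoint, "health-related quality of life assessed by the EQ-5D (EuroQoL) at 2 years". The Discussion, under Patient reported outcome measurements, says "The trial’s main outcome measurements are Harris hip score and EQ-5D".

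The lists of secondary outcomes agree with that. The Background states "The secondary outcome measurement includes mortality, complications and reoperations", without EQ-5D, and Table 2 does not list it either. Endpoints and follow-up adds only functional scores at time points other than the primary one.

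The Sample size section differs. It plans the Harris hip score on a two-sided test of equal means (difference 10 points, SD 15) and states 80 % power with 40 per group. It then claims 80 % power for non-inferiority "of the secondary endpoint EQ-5D with a sample of 40 patients in each group". On the level it says: "The significance level was set at a conservative 2.5 % (p <0.025) because we have two sample size calculations". Enrolment is 60 per group to allow for loss.

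**The concern.** The section that fixes alpha and sample size gives EQ-5D a different rank from the rest of the article. The rank decides what the 2.5 % is for:

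- If either of two primary endpoints can support a claim by itself, a split or an equivalent procedure is required.
- If the Harris hip score is the only primary endpoint, no split is needed and 2.5 % is a voluntary strictness.

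The number of sample size calculations does not decide between these; the number of tests that can each support a claim does. The article never says whether success means the Harris hip score alone, either endpoint, or both. After the 2-year data are in, one analyst could cite the Abstract to claim success on EQ-5D alone, and another could cite the Sample size section to call the same result secondary.

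The EQ-5D hypothesis also moves. The Background expects superior quality of life, whereas the Sample size section plans for non-inferiority. A non-inferiority result and a superiority result support different claims.

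**Working it through.** **1. Role of EQ-5D by section**

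| Section | Role |
|---|---|
| Abstract, Methods/Design | primary |
| Endpoints and follow-up | part of the primary endpoint, at 2 years |
| Discussion, Patient reported outcome measurements | main outcome |
| Background and Table 2 (secondary outcomes) | not listed |
| Sample size | secondary |

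Most of the text supports the co-primary reading. The halved alpha fits it too.

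**2. Error rate on the printed plan**

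Only one level is printed, 2.5 %. Used for each of two tests, the chance of at least one false positive is at most 0.025 + 0.025 = 0.05 under any correlation. If the tests were independent it would be 1 − 0.975² = 0.0494. This holds whichever label EQ-5D carries.

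**3. The stated Harris hip score calculation**

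Inputs, all from Sample size: difference δ = 10, SD σ = 15, two-sided, 40 per group, 80 % power, level 2.5 %. The Statistics section names the t-test, and allocation is 1:1.

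Normal approximation: n per group = 2σ²(z₁₋α/₂ + z₀.₈)²/δ², where 2σ²/δ² = 2 × 225/100 = 4.5.

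- α = 0.025: 4.5 × (2.2414 + 0.8416)² = 42.8, so 43. Exact t-test: 44.05, so 45.
- α = 0.05: 4.5 × (1.9600 + 0.8416)² = 35.3, so 36. Exact t-test: 36.3, so 37.

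Power with 40 per group: the standard error is 15 × √(2/40) = 3.354, and 10/3.354 = 2.981.

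- α = 0.025: Φ(2.981 − 2.241) = 77.0 %. Exact t-test: 75.5 %.
- α = 0.05: Φ(2.981 − 1.960) = 84.7 %. Exact t-test: 83.8 %.

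The stated pair (40 per group, 80 %) is not reproduced at either level. Forty per group exceeds 80 % at two-sided 5 % and falls short of it at the printed 2.5 %.

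**4. Does enrolment cover it?**

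The step from 40 to 60 per group implies an allowance of 1 − 40/60 = 33 % loss. With 45 needed (2.5 %) the tolerable loss is 1 − 45/60 = 25 %. With 37 needed (5 %) it is 1 − 37/60 = 38 %. With no loss, 60 per group gives 91.5 % power at 2.5 % (t-test).

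**The case against.** The strongest reply is that this is one wrong word. Three sections make EQ-5D primary or main, no secondary list names it, and halving alpha is what one does for two primary endpoints. The level is printed once and openly described as conservative, which is a permissible choice. A success rule may also stand in an analysis plan that is not shown. Much of this stands: the co-primary reading is the likelier one, and the printed level controls error. But an analysis plan could only choose between the two roles; the article would still be wrong in one place. The shortfall in power at 2.5 % is independent of the label.

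A reader might infer more than the text supports:

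- *That the Harris hip score has two contradictory alphas, so p = 0.03 could be success or failure.* Only 2.5 % is printed, and p = 0.03 misses it under either label. It succeeds only if the stated level is set aside.
- *That the false-positive risk is about 9 %.* That figure (9.1 % at an assumed correlation of 0.5; 9.75 % if independent) describes testing both endpoints at 5 %, which the article nowhere proposes.
- *That the Statistics section adds to the conflict by planning ANCOVA for a primary endpoint in the singular.* Endpoints and follow-up also uses the singular while naming both outcomes, so this is the authors' usage and no separate evidence.
- *That the trial is underpowered.* The 60 enrolled per group leave room under either reading.

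**Conclusion.** The point holds as an internal contradiction about the role of EQ-5D. Its consequences are that the success rule is not fixed and the purpose of the 2.5 % level is unclear. It is not a finding of inflated type I error.

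The measurable part is the Harris hip score calculation: 75.5 % power at the printed level with 40 per group, about 4.5 percentage points below the stated 80 %, or 5 patients per group short of the 45 needed. This rests on the printed difference and SD, equal groups, a t-test, and 2.5 % being two-sided, as the section's description of its power analysis implies. Were 2.5 % meant as one-sided, 40 per group would give 83.8 % and the shortfall would vanish, but the text does not say so. The correction should be made; it does not threaten the planned enrolment unless loss exceeds about 25 %.

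**What to change.** Give EQ-5D one role in every section, and settle it before the 2-year data are analysed.

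- **If co-primary (the reading most of the text supports):** delete the word secondary for EQ-5D in Sample size. State that either endpoint can support its own claim within a total alpha of 5 %. Replace the fixed split by Holm: the smaller p-value against 2.5 % and, if that is significant, the other against 5 %. The fixed split is already valid, but Holm controls the same error and can never reject less. Restate the Harris hip score sample size as 45 per group for 80 % power at 2.5 %, or keep 40 and state power of about 75 %.
- **If the Harris hip score is the sole primary endpoint:** say so in the Abstract, the endpoints section and the Discussion. Test it at two-sided 5 % (37 per group for 80 %; 40 give 83.8 %), and test EQ-5D at 5 % only if the Harris hip score is significant.

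In both cases, reconcile the superiority hypothesis in the Background with the non-inferiority aim in Sample size, because the EQ-5D p-value is undefined until that is done. Claim benefit on EQ-5D only from a superiority test.

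The cost is small but not wording alone: one sample size or power figure must be restated and one hypothesis decided. Enrolment of 120 need not change.

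### If Harris hip score and EQ-5D are confirmed as joint primary endpoints, Holm's step-down would spend the same 5 % family error more efficiently than a fixed 2.5 % per test

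*Protocol article*

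**What the plan says.** The level is set in the Sample size section: "The significance level was set at a conservative 2.5 % (p <0.025) because we have two sample size calculations". No condition is attached to it. The Statistics section plans a t-test for each of the two scores, with no level, order or step-down.

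On the status of the two outcomes the article is not consistent:

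- The abstract (Methods/Design) says: "The primary endpoints are Harris hip Score and EQ-5D".
- The section Endpoints and follow-up puts both under the primary endpoint at 2 years, and the Discussion section on patient-reported outcomes treats both as the main measures.
- The hypothesis at the end of the Background is that total hip arthroplasty "results in superior hip function and health-related quality of life".
- The Sample size section, which sets the 2.5 %, instead claims "80 % power to prove non-inferiority (non- difference) of the secondary endpoint EQ-5D with a sample of 40 patients in each group". It gives a mean of 0.73 and an SD of 0.18, but no margin.

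For Harris hip score the same section takes a difference of 10 points with SD 15, describes a two-sided power analysis, and concludes: "We calculate that a total of 80 patients (40 in each group) will have a power of 80 % to yield a significant result".

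**The concern.** Giving each of two tests half of 5 % is a Bonferroni split. It holds the family error, but once one test has succeeded it makes no use of the level that this success releases. Holm's rule does: it tests the larger p-value at 5 % after the smaller has passed at 2.5 %.

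At stake are results where one endpoint has passed and the other has a p-value between 0.025 and 0.05. As the rule is written, such a second endpoint is declared not significant; under Holm it is a success. The hypothesis expects a benefit on both hip function and quality of life, and that is the situation in which the difference matters. The plan also has little power to spare: at two-sided 2.5 %, the 40 per group that it is built on falls somewhat short of 80 % for Harris hip score.

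**Working it through.** **1. The plan's own figure.** Inputs from the Sample size section: difference 10, SD 15, two-sided test, power 80 %, 40 per group.

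n per arm = 2 × (z₁₋α/₂ + z₀.₈)² × SD² / difference²

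- α = 0.025: 2 × (2.241 + 0.842)² × 225 / 100 = 42.8, so 43 (45 with the exact t distribution).
- α = 0.05: 2 × (1.960 + 0.842)² × 225 / 100 = 35.3, so 36 (37 with t).

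Power with 40 per arm: the standard error is 15 × √(2/40) = 3.354, and 10 / 3.354 = 2.981.

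- α = 0.025: Φ(2.981 − 2.241) = 77.0 % (75.5 % with t).
- α = 0.05: Φ(2.981 − 1.960) = 84.7 % (83.8 % with t).

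The stated 40 for 80 % is reproduced at neither level. At two-sided 2.5 % it is slightly too small.

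**2. Error control.** Fixed split: 0.025 + 0.025 = 0.05 at most, or 1 − 0.975² = 0.0494 if the tests are independent. Holm:

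- Both nulls true: a false rejection needs the smaller p-value below 0.025, so its probability is at most 0.025 + 0.025 = 0.05.
- One null true: it is never rejected unless its own p-value is below 0.05, so the probability is at most 0.05.

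This holds under any correlation. In simulation with both nulls true, the family error was the same for the two rules, 4.3-5.0 %.

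**3. Dominance.** Any p-value below 0.025 is rejected under both rules. Holm adds only the case where one p-value is below 0.025 and the other lies between 0.025 and 0.05. The event of at least one success is therefore identical under the two rules. Since P(Harris) + P(EQ-5D) = P(at least one) + P(both), the gain for both equals the sum of the two separate gains.

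**4. Size.** Simulated two-sided t-tests, 40 per arm, Harris hip score 10 / 15. Assumed, because the article gives neither: true EQ-5D difference 0.10 (SD 0.18) and correlation 0.5.

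| | Fixed 2.5 % | Holm | Gain (points) |
|---|---|---|---|
| Harris hip score | 75.5 % | 78.9 % | 3.4 |
| EQ-5D | 58.2 % | 66.1 % | 7.9 |
| Both | 50.2 % | 61.5 % | 11.3 |

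Check: 3.4 + 7.9 = 11.3.

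Over EQ-5D differences of 0.08-0.12 and correlations of 0.3-0.7, the gains are about 1-6 points for Harris hip score, 5-10 for EQ-5D and 9-12 for both. If all 60 per arm were analysed, the gain for both would be about 5-11 points.

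**5. Other assumptions.** A second simulation used z-tests, 40 per arm, correlation 0-0.7, and an EQ-5D difference of 0.124. That is the difference with 80 % power at two-sided 2.5 %: (2.241 + 0.842) × 0.18 × √(2/40) = 0.124.

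- Harris hip score: 77.0 % to 81.8-83.1 %.
- EQ-5D: 80.0 % to 83.7-85.3 %.
- Both: 61.6-69.3 % to 73.0-77.8 %.
- At least one: 87.7-95.4 % under either rule.

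The EQ-5D effect here has the same standardised size as a non-inferiority test with a margin of 0.124 and no true difference. That margin is only what 40 per arm would imply at one-sided 1.25 %; the article states none.

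If only the Harris hip score effect is real and EQ-5D is tested for a difference, Harris hip score power goes from 77.1 % to 77.2-77.3 %.

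**The case against.** The strongest reply is that nothing here is wrong. Two tests at 2.5 % control the family error, the article openly calls the level conservative, and single-step testing gives simple intervals that always agree with the decisions. That stands: this is a gain in efficiency, not the repair of an invalid analysis.

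Second, the premise is unsettled. The section that sets the level calls EQ-5D secondary and plans it as non-inferiority. If it is secondary, the primary level needs no split. If success required both endpoints, each could be tested at 5 % and Holm would itself be too strict. This stands as a condition. Still, most of the article treats both as primary or main, and splitting the level makes sense only if both are confirmatory.

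Third, a reader might infer that the article binds the second test to 0.025 whatever the first shows. It does not say so in words; it prints a threshold without a condition. A sample size planned at 0.025 is also compatible with Holm, whose first step uses that level. The unconditional reading is the natural one for a printed rule, but it remains a reading.

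Fourth, a reader might conclude that power is given away for nothing. That goes too far. The chance of at least one success does not move, the largest gain concerns winning both, which the article does not make its success criterion, and the gains depend on an EQ-5D effect and a correlation that it does not give.

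**Conclusion.** As written, the 2.5 % rule is a valid but inefficient single-step Bonferroni split. If both outcomes are confirmed as alternative primary endpoints, Holm is at least as powerful for each of them at the same 5 % family error, whatever their correlation. That conclusion needs no assumption about effect sizes.

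The size of the gain does: a true effect on both outcomes, 40 analysed per arm, and the assumed ranges for the EQ-5D difference and the correlation. Within those ranges the benefit is modest for each endpoint and larger for winning both. It is close to nil for Harris hip score when EQ-5D is tested for a difference that does not exist.

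The documents do not support reading this as a failure of error control. The conflict over the status of EQ-5D, and the missing margin if non-inferiority is meant, come first; Holm resolves neither.

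**What to change.** First state whether EQ-5D is primary or secondary, and make the abstract, the endpoint section and the Sample size section agree.

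- **If both are primary and either alone counts as success:** replace the fixed threshold with a sentence such as: The two primary p-values are ordered; the smaller is tested at 0.025 and, if it is significant, the larger is tested at 0.05 (Holm). If EQ-5D is tested one-sided for non-inferiority, state the margin and enter twice the one-sided p-value.
- **If EQ-5D is secondary:** drop the split and test Harris hip score at two-sided 5 %, where 40 per arm gives 83.8-84.7 % power.

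The cost is one sentence, with no added patients or data, provided that it is fixed before the two-year results are seen. There is one small downside: if 97.5 % intervals are reported for both endpoints, the interval for the second may include no difference (or, for non-inferiority, the margin) although Holm declares success. A footnote can explain this.

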### Statistics

The analyses will be performed on the basis of the intention-to-treat principle, and all patients who are allocated to either group will be included in the analysis, regardless of actual surgery performed. Descriptive statistics (means and standard deviations) will be used to describe the patient characteristics and outcome variables at the measurement points. We will use the Student’s t-test and Levene’s test for comparison of Harris hips score and EQ-5D between the groups. An analysis of covariance (ANCOVA) of the primary endpoint will also be used to reduce variance, adjusted for exposure variable (total hip arthroplasty/hemiarthroplasty) and stratification (male/female). For subjects that withdrawn from the study before completion, the data from the last observation will be carried forward (imputed). The analyses will be performed with SPSS 22.0 for Windows (SPSS, Chicago, Illinois) statistical software.

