## Abstract

**Background:**

A femoral neck fracture (FNF) is a common cause of suffering and premature death in the elderly population. Optimizing the treatment for improved outcome and a reduced need for secondary surgery is important both for the patient and the society. The choice of primary total or hemiarthroplasty in patients over eighty years are controversial. We hypothesized that total hip arthroplasty has an equal or better outcome in patient-reported outcome compared with hemiarthroplasty.

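### Analysing every endpoint by allocation only is cautious for a superiority test but favours the EQ-5D non-inferiority claim if patients receive the other implant

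*Protocol article*

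**What the plan says.** The Statistics section of the protocol article opens with a general rule: "The analyses will be performed on the basis of the intention-to-treat principle". It spells out what this means when the operation differs from the allocation: "all patients who are allocated to either group will be included in the analysis, regardless of actual surgery performed". EQ-5D is not excepted, and the article describes no analysis by implant received.

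The article states its EQ-5D aim in more than one way:

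- Sample size claims "80 % power to prove non-inferiority (non- difference) of the secondary endpoint EQ-5D", "with a sample of 40 patients in each group" and an "assumption of an EQ-5D value of 0.73 with standard deviation 0:18". No margin is given.
- The Abstract hypothesises that "total hip arthroplasty has an equal or better outcome in patient-reported outcome compared with hemiarthroplasty".
- The last paragraph of Background words the hypothesis as superiority of total hip arthroplasty, for hip function and for quality of life.
- Endpoints and follow-up puts EQ-5D at 2 years in the primary endpoint, while Sample size calls it secondary.
- Statistics names a Student's t-test for both scores, with no comparison of a confidence limit against a margin.

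**The concern.** One population rule serves two opposite inferential aims. A patient who receives the other arm's implant but is counted by allocation pulls the two group means together. In a test for a difference this costs power and does not create false positives. In a non-inferiority test a true deficit looks smaller than it is, so the claim succeeds too often.

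At stake is a conclusion that quality of life after one implant is no worse than after the other, reached partly because some patients in the two arms had the same implant. The article chooses the analysis population and says how switched patients are counted, so this is a stated choice and not merely a detail left to another document.

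**Working it through.** **Inputs from the Sample size section:** SD 0.18; 40 per group; power 80 %; significance level 2.5 %; 60 per group enrolled.

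**Assumptions, because the article gives no figure:** the non-inferiority margin M; the test taken as one-sided 2.5 %; the share c of patients given the other implant; and switched patients having the expected EQ-5D of the implant they received.

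**Step 1: the plan's own figure.** The 40 per group cannot be reproduced for EQ-5D without a margin. It can only be inverted to find the margin that it implies:

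- SE = 0.18 × √(2/40) = 0.0402
- M = (1.960 + 0.8416) × 0.0402 = 0.1128, about 0.113

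At one-sided 1.25 % the implied margin would be 0.124, and at one-sided 5 % it would be 0.100.

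**Step 2: dilution.** If the true deficit is M, the expected by-allocation deficit is M(1 − c) with switching in one arm and M(1 − 2c) with the same share switching in both arms.

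**Step 3: false-claim rate.** The non-inferiority test then succeeds with probability

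- one arm: Φ(c × M/SE − 1.960)
- both arms: Φ(2c × M/SE − 1.960)

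With 40 per arm M/SE = 2.8016. For example, c = 5 % in both arms gives Φ(0.280 − 1.960) = Φ(−1.680), about 4.6 % (4.65 % to two decimals). For c = 10 % in both arms, Φ(0.560 − 1.960) = Φ(−1.400), about 8.1 %.

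If all 60 enrolled per arm are analysed with the same margin, SE = 0.18 × √(2/60) = 0.0329 and M/SE = 3.431.

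| Switched at surgery | 40 per arm, one arm | 40 per arm, both arms | 60 per arm, one arm | 60 per arm, both arms |
|---|---|---|---|---|
| 0 % | 2.5 % | 2.5 % | 2.5 % | 2.5 % |
| 2 % | 2.8 % | 3.2 % | 2.9 % | 3.4 % |
| 5 % | 3.4 % | 4.6 % | 3.7 % | 5.3 % |
| 10 % | 4.6 % | 8.1 % | 5.3 % | 10.1 % |

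**Step 4: sensitivity to the assumptions.**

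- A smaller assumed margin of 0.05, with 10 % switching and 40 per arm, gives 3.3 % (one arm) or about 4.3 % (both arms).
- Sample size speaks of a two-sided analysis at 2.5 %. If that means one-sided 1.25 %, M/SE = 2.2414 + 0.8416 = 3.083. Then 5 % switching gives 1.8 % or 2.7 %, and 10 % gives 2.7 % or 5.2 %, against a nominal 1.25 %.

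The direction is the same in every case; only the size changes.

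**The case against.** The strongest reply is that intention to treat is correct and that a supporting per-protocol analysis is commonly set in an analysis plan, which is not shown here. The first half stands: a reader might infer that the by-allocation analysis is an error, and it is not. The second half stands in part. An unseen plan could add the analysis, and the article does not forbid it. Still, the article fixes one rule for its analyses while stating a powered non-inferiority aim, and makes no separate provision for that aim.

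A second reply is that the direction depends on which EQ-5D hypothesis is tested. This stands. A reader might infer that the by-allocation rule weakens the EQ-5D result whatever margin or test is used. The documents do not support that: the only test named is a t-test, Background words EQ-5D as superiority, and for such a test the rule is conservative. The point applies only to the non-inferiority claim. The missing margin and the conflicting hypotheses are separate and larger gaps, but closing them would not remove the dilution.

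A third reply is that switching may be rare. This also stands. Treatment is a single index operation, and Discussion (Study design) says that the exclusions mainly target malignant disease or contraindications to either method. A reader might take the phrase about the surgery actually performed as a sign that switching is expected, but it is ordinary intention-to-treat wording and implies no rate. At 1 % in both arms the false-claim rate is 2.8 %.

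Last, a true deficit as large as the margin runs against the authors' expectation. That does not count against the calculation: a false-claim rate is evaluated at the margin by definition and is not a forecast.

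**Conclusion.** The point holds in a limited form. Counting every patient by allocation is conservative for the Harris hip score and for EQ-5D if it is tested for superiority, but anti-conservative for the EQ-5D non-inferiority claim that Sample size powers.

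The direction is firm. The size is conditional on the assumed margin, the sidedness of the test, a true deficit at the margin and, above all, an unknown switching rate. Inflation is modest at a few per cent switching, exceeds a tripling of the nominal 2.5 % at 10 % in both arms (8.1 %), and vanishes without switching. This is an inexpensive improvement to the plan and not a flaw that invalidates it.

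**What to change.** Keep intention to treat as the main analysis for both endpoints. If EQ-5D non-inferiority is to be claimed, add to the Statistics section:

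- a supporting EQ-5D analysis restricted to patients who received the allocated implant at the index operation;
- missing data handled as in the main analysis, so that no further selection on completed follow-up is introduced;
- later conversions kept in the allocated arm, as a consequence of the allocated treatment;
- the number switched at surgery, reported by arm;
- a statement that non-inferiority is claimed only if the two analyses are consistent, with consistency defined in advance, for example as both confidence limits clearing the margin. This needs a stated margin.

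The cost is a few lines of text and one extra analysis on data already collected; no sample size, treatment or visit changes. There are two downsides. First, the chance of claiming non-inferiority falls. If 10 % are removed from each arm of 40, leaving 36, the supporting analysis has SE = 0.18 × √(2/36) = 0.0424 and, with no true difference, power Φ(0.1128/0.0424 − 1.960) = Φ(0.698), about 76 % instead of 80 %. Requiring both limits to clear the margin cannot do better than that. Second, the restricted set is not fully protected by randomisation and its bias can go either way, so it supplements intention to treat and does not replace it.

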### Randomization and blinding

Patients will be randomized in a 1:1 ratio to hemiarthroplasty or total hip arthroplasty using concealed envelopes in batch sizes of 10. Randomization will be stratified for gender and patients will be blinded for the assigned treatment during the first two years of follow-up. Patients will not be allowed to view x-rays. Ward staff and physiotherapists are aware of allocations but are mindful that patients are blinded and are encouraged not to speak to patients about allocation. The physiotherapy, nor any other in-hospital care, do not differ between the two groups. In addition, the blinding will be controlled for at the 1 and 2 year follow-up where patients will be asked what group they think they belong to. The blinding is ended at the 2-year follow-up and in case of any hip related serious adverse events such as reoperations for any reasons.

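### The primary endpoint gets both an unadjusted t-test and a sex-adjusted ANCOVA, and the article does not say which decides (minor)

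*Protocol article*

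**What the plan says.** The Randomization and blinding section of the protocol article states: "Randomization will be stratified for gender". Allocation is 1:1, "using concealed envelopes in batch sizes of 10".

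The Statistics section gives two analyses. The first is unadjusted: "We will use the Student’s t-test and Levene’s test for comparison of Harris hips score and EQ-5D between the groups". The second is adjusted: "An analysis of covariance (ANCOVA) of the primary endpoint will also be used to reduce variance", and its terms are "adjusted for exposure variable (total hip arthroplasty/hemiarthroplasty) and stratification (male/female". Neither is called primary, supportive or a sensitivity analysis.

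The Sample size section says that "a two-sided power analysis has been performed", on the inputs "We assume that a mean difference of 10 points (standard deviation, 15 points". It sets the significance level at 2.5 %, with the reason "p <0.025) because we have two sample size calculations". Those two calculations are for HHS and for EQ-5D.

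**The concern.** The t-test ignores the factor on which allocation was balanced, and the ANCOVA includes it. If sex predicts HHS, the two give different standard errors and can fall on opposite sides of 0.025. With no stated order, the result that counts could then be chosen after both are known. The reduced significance level offers no protection, because it was set for two endpoints and not for two tests of one endpoint.

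The stated purpose of the ANCOVA is to reduce variance. Leaving it as an unranked addition means the article does not commit to the analysis that would serve that purpose.

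**Working it through.** **Inputs from the article.** Difference 10 points, SD 15, two-sided level 0.025, 40 evaluable per arm, 60 enrolled per arm, randomisation stratified by sex in batches of 10 (read as blocks).

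**Assumptions.** 25 % men; male-female HHS difference d of 0 to 10 points, with 15 shown as an extreme. The article gives neither figure, nor any R².

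**Step 1: the article's own figure.** n per arm = 2 (z + 0.842)² × 15² / 10².
- Two-sided 2.5 %: 2 × (2.241 + 0.842)² × 2.25 = 42.8, so 43 per arm (45 with the t distribution).
- Two-sided 5 %: 2 × (1.960 + 0.842)² × 2.25 = 35.3, so 36 per arm (37 with the t distribution).

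The stated 40 per arm for 80 % power is not reproduced at either level. At 40 per arm and two-sided 2.5 %, power is 77.0 % by the normal approximation and 75.5 % by noncentral t. That is a separate matter; 75.5 % is the baseline used in step 4.

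**Step 2: standard errors of the two tests.** Share of variance due to sex: R² = d² × 0.25 × 0.75 / (225 + d² × 0.25 × 0.75). For d = 10 this is 18.75 / 243.75 = 0.077. With allocation balanced within sex, the t-test standard error should exceed the ANCOVA one by a factor of about 1/√(1 − R²). For d = 10 that is 1/√0.923 = 1.04.

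Simulation with sex-stratified blocks of 10, 40 per arm, no loss and within-sex SD 15 gave:

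| d (points) | R² | SE t-test / ANCOVA (null) | Type I, t-test | Type I, ANCOVA | Power, t-test | Power, ANCOVA |
|---|---|---|---|---|---|---|
| 0 | 0 | 3.339 / 3.340 | 0.0254 | 0.0253 | 75.3 % | 75.2 % |
| 3 | 0.007 | 3.359 / 3.348 | 0.0236 | 0.0240 | 75.6 % | 75.5 % |
| 5 | 0.020 | 3.377 / 3.344 | 0.0238 | 0.0246 | 75.5 % | 76.2 % |
| 10 | 0.077 | 3.484 / 3.347 | 0.0187 | 0.0248 | 73.5 % | 76.5 % |
| 15 | 0.158 | 3.651 / 3.348 | 0.0166 | 0.0282 | 68.3 % | 75.5 % |

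The Monte Carlo error on the type I figures is about 0.0014. The t-test loses about 1 % of its standard error or less up to d = 5, and 4 % at d = 10. It errs on the conservative side.

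**Step 3: two unranked p-values.** With one third of 120 patients lost at random and d from 0 to 10, rejecting if either test is significant gives a type I error of about 2.6-2.9 %. With a true difference of 10 points, the tests disagree in about 1.5-5 % of trials. With no loss, disagreement is about 0.9, 1.6 and 3.5 % at d = 0, 5 and 10.

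**Step 4: what adjustment could add.** Hold the total SD at 15 and let the covariates explain R², so that the residual SD is 15√(1 − R²). Noncentral t, 40 per arm, two-sided 2.5 %:
- R² = 0: noncentrality 10 / (15 × √(2/40)) = 2.98, power 75.5 %.
- R² = 0.05: residual SD 14.62, power 77.9 %.
- R² = 0.10: residual SD 14.23, power 80.2 %.

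These R² values are an assumed range for sex and age together. They are not estimates for sex alone.

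**The case against.** The strongest reply is that the article already plans the sex-adjusted analysis, and that ranking analyses is ordinary content for an analysis plan that is not shown. The first half stands: the stratification factor has not been overlooked. The second half stands only in part. The article itself commits to two tests of the same endpoint, so the ambiguity lies in its own text. If a fuller plan already ranks them, the article needs only to match it.

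Four stronger readings are tempting and are not supported:

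- **That precision is wasted in the headline test.** The t-test is named first but never called primary. The loss depends on an unstated link between sex and HHS. It becomes material only at a male-female gap of about 10 points, as large as the smallest effect that the article treats as clinically relevant.
- **That taking the better p-value pushes the error rate to around 3 % or above.** This needs the two tests to be correlated at about 0.95 to 0.985, which is close to the unstratified case (0.990, 0.983 and 0.950 at d = 3, 5 and 10). With sex-stratified blocks and one third lost, the correlations are 0.996, 0.994 and 0.981, and the inflation is smaller.
- **That Levene's test chooses between two t-tests.** The article lists it beside the t-test and describes no such rule.
- **That leaving age out of the ANCOVA is an error.** Adjusting for the stratification factor alone is legitimate. All patients are in a narrow age band, and nothing in the article says how strongly age predicts HHS. Adding age is an improvement on offer.

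**Conclusion.** The point holds as a minor one. The article fixes two analyses of its primary endpoint and leaves open which decides, and the 2.5 % level was not set to cover that choice. The consequence is limited: an either-test type I error of about 2.6-2.9 % instead of 2.5 %, discordant results in about 1.5-5 % of trials when the true difference is 10 points, and a mildly conservative t-test if sex predicts HHS. From sex alone, choosing the adjusted model gains about 0 to 3 points of power.

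These sizes rest on 25 % men, male-female differences of 0 to 10 points and random loss of one third. The existence of two unranked p-values rests on no assumption; it can be read from the Statistics section.

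**What to change.** In the Statistics section, name one primary analysis for both HHS and EQ-5D at 2 years: a linear model with treatment, sex (the stratification factor) and age as a prespecified covariate. State that its treatment effect and p-value decide, and that the t-test is supportive. Naming both outcomes also settles whether the adjusted model applies to EQ-5D, which the Endpoints section treats as primary and the Sample size section calls secondary. If Levene's test is kept, say what it is for.

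The cost is about one sentence. Sex and age are known for every patient at inclusion, so no new data or patients are needed. The change should be dated before any unblinded comparison of the 2-year results.
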